## Abstract

**Background:**

Two out of three neonatal deaths occur in just 10 countries and Pakistan stands third among them. Maternal mortality is also high with most deaths occurring during labor, birth, and first few hours after birth. Enhanced access and utilization of skilled delivery and emergency obstetric care is the demonstrated strategy in reducing maternal and neonatal mortality. This trial aims to compare reduction in neonate mortality and utilization of available safe birthing and Emergency Obstetric and Neonatal Care services among pregnant mothers receiving ‘structured birth planning’, and/or ‘transport facilitation’ compared to routine care.

**Methods:**

A pragmatic cluster randomized trial, with qualitative and economic studies, will be conducted in Jhang, Chiniot and Khanewal districts of Punjab, Pakistan, from February 2011 to May 2013. At least 29,295 pregnancies will be registered in the three arms, seven clusters per arm; 1) structured birth planning and travel facilitation, 2) structured birth planning, and 3) control arm. Trial will be conducted through the Lady Health Worker program. Main outcomes are difference in neonatal mortality and service utilization; maternal mortality being the secondary outcome. Cluster level analysis will be done according to intention-to-treat.

**Discussion:**

A nationwide network of about 100,000 lady health workers is already involved in antenatal and postnatal care of pregnant women. They also act as “gatekeepers” for the child birthing services. This gate keeping role mainly includes counseling and referral for skill birth attendance and travel arrangements for emergency obstetric care (if required). The review of current arrangements and practices show that the care delivery process needs enhancement to include adequate information provision as well as informed “decision” making and planned “action” by the pregnant women. The proposed three-year research is to develop, through national technical working group process, and then test a set of arrangements for achieving the enhanced utilization of safe birthing services.

**Trial registration:**

Current Controlled Trials ISRCTN86264432

## Background

### Burden of Neonatal and maternal mortality in Pakistan

Around four out of 30 million infants born each year worldwide die in the first 28 days of life and more than one quarter of deaths occur in the first 24 hours of birth [1,2]. Two out of three neonatal deaths occur in just 10 countries and Pakistan stands third among these countries [1]. In Pakistan the newborn mortality is 55 deaths per 1000 live births, infant mortality rate is 77 deaths per 1000 live births and maternal mortality ratio is 276 per 100,000 live births [3]. The new born babies and infants die mainly due to birth asphyxia, intra-uterine growth retardation, and acute infections [3-5]. The major causes of maternal deaths are hemorrhage, obstructed labor, puerperal sepsis and toxemia of pregnancy. Most of these causes are both preventable and treatable.

### Continuum of care during pregnancy

Throughout the continuum of care, the period with the highest risk of death and disability for both mother and newborn is labor, birth, and the first few hours after birth. Hence the health and survival of mother and newborn are closely linked to care the mother receives before and during childbirth and during the immediate postnatal period. There is an inverse relationship between the proportion of deliveries assisted by a skilled birth attendant and the maternal mortality ratio in developing countries [6]. Enhanced access and utilization of skilled delivery care and emergency obstetric and neonatal care (EmONC) is the demonstrated strategy in countries that have succeeded in reducing maternal and neonatal mortality [7].

Studies on maternal mortality have identified the need for addressing the three delays in accessing emergency obstetric care and for integrated efforts for saving mothers’ lives both at the community and hospital level [8]. The past investments in expanded health care infrastructure have brought the services closer to the people but still majority of births occur at home and are attended by untrained traditional birth attendants [3].

### Maternal, Newborn and Child Health (MNCH) and Lady Health Worker (LHW) program in Pakistan

The Government of Pakistan has launched the Maternal, Newborn and Child Health (MNCH) Programme to address service availability and the utilization gaps, by building on the already existing experiences, initiatives and resources. The main objectives of the MNCH Programme, to be achieved by 2015, include: reducing the newborn mortality to less than 40 per 1000 live births and maternal mortality ratio to less than 140 per 100,000 live births [9]. The MNCH Programme, in accordance with the national policy, emphasizes prenatal, postnatal and newborn care, birth preparedness, skilled birth attendance, and strengthening the primary and secondary level of health care [9]. Making birth practices safer for mother and newborn is the key programme strategy for achieving the desired reduction in the maternal and newborn mortality. The Lady Health Worker (LHW) Programme evaluation has shown a reasonable coverage and uptake of LHW antenatal services in their respective communities. National Maternal and Child Health Policy and Strategic Framework (2005–2015) identifies LHWs as the core actor in addressing decision and access delays to safe child birthing [9]. So in addition to providing antenatal and postnatal services to pregnant women, LHWs also act as a ‘gate-keeper’ for safe birthing services. The LHWs carry out this gate keeping role through birth-preparedness planning (BPP) and complication-readiness planning (CRP) with pregnant women and their family members [10,11]. Currently, LHWs lack structured guidelines and tools to carry out counseling, planning and facilitation for the gate-keeping role.

### Rationale and Objectives

The proposed research exercise will focus on innovative operations and materials to reduce neonatal mortality and optimize the utilization of safe birthing services and the basic and comprehensive EmONC services being made available at the rural health centers and hospitals. The two main dimensions of the intervention to be developed and tested are: a) Enabling the pregnant women and families to plan and prepare for ‘safe birth’ and ‘EmONC’ (i.e. address the delay in decision-making); b) Mobilizing the communities to arrange travel for emergency obstetric care (i.e. address the delay in timely access).

The experience and the products of this research will help to strengthen the linkages between the LHW and MNCH programmes, in a holistic way and to build the district and programme capacity to implement these interventions under routine programme circumstances.

#### Specific objectives

 · To compare the neonatal mortality in the intervention arms as compared to the control arm.

 · To compare the utilization of safe birthing services and the basic and comprehensive EmONC services in the intervention arms as compared to the control arm.

 · To compare the maternal mortality in the intervention arms as compared to the control arm.

 · To compare the health services and the patient costs of the three selected strategies in achieving the desirable service utilization and pregnancy outcomes, and to assess the feasibility of addressing the “decision” and “access” delays in the context of the national programme in Pakistan.

 · To understand the attitudes, the social pressures (subjective norms) and the enabling factors (environment: services access and quality, time, money etc.,) that influenced the decisions and ability of pregnant women and their families to utilize the available safe birthing and EmONC services, and to suggest further improvements for the utilization of MNCH services in Pakistan.

## Methods

### Study Design

A pragmatic parallel arms cluster randomized controlled trial (c RCT) with three arms will be conducted from February 2011 to May 2013. Pregnant females in arm 1 will be given interventions to address decision delay plus the access delay. Those in trial arm 2 will be given intervention to address decision delay only. Trial arm 3 will be the control arm (routine care of the pregnant females by the LHWs) (Figure 1).

**Figure 1 F1:**
[figure not shown]
Flow of the trial.

### Interventions

The ‘structured birth planning’ intervention is to address the decision delays for safe birthing, whereas ‘transport facilitation’ intervention is to address the access delays for EmONC services.

#### Structured Birth Planning

This event, with the help of a specially designed communication guide/tool, will provide the pregnant women and family members with the required knowledge (technical, administrative and costs) and facilitate them to take informed decisions regarding safe birthing and EmONC services as required. This communication will provide the client information regarding all the available and qualified birthing service providers, in the order of programme guided preference (i.e. facility-based doctors and Lady Health Visitor (LHV), community-based Community Mid Wife (CMW), and private clinics). The agreed choice will be recorded, and pregnant women will be provided with an information package relevant to her decisions and subsequent actions.

#### Transport facilitation

The proposed intervention is a facilitated travel arrangement for pregnant woman who need to access EmONC services at the designated facility. The intervention is to ensure that the affordable (even subsidized or free for the deserving/poor women) transport facility is available in-time for the pregnant woman to access the EmONC services, when required. The arrangements for facilitated travel for EmONC will be discussed, agreed and documented during initial interaction between the pregnant woman and her lady health worker. The detailed modalities (including transport selection, subsidy, payment, communication etc.) for managing this service will be developed in consultation with districts, facilities and communities during the first few months of the proposed project. The role of EmONC facility staff in establishing and managing the travel-facilitation will be encouraged.

#### Mapping of skilled birth attendants, EmONC facilities and transport providers

In each of the selected intervention cluster, the mapping exercise will be carried out through the respective LHWs. This mapping exercise will focus on available skilled birth attendants and EmONC facilities plus available travel services in the clusters. The access, quality and cost dimensions of these available service options will be considered for a pregnant woman and family to make an informed choice. The research intervention will also supplement (but neither duplicate nor expand) the programme EmONC facility strengthening inputs, where needed.

The data collected from the mapping exercise will be organized in form of directories (Birth providers directory, transport providers directory & EmONC facilities directory) and used in the communication with pregnant women in the respective cluster. Safe birthing planning, by pregnant woman and her family, will be carried out by the LHW with each identified pregnancy in her respective locality by specially designed pictorial tool. Each woman in a cluster will be offered the same care package. As LHWs are the source to deliver the trial intervention, the chances of inter-cluster contamination are considered reasonably low.

### Outcome indicators

Two main outcome indicators to be used in the trial are pregnancy outcomes and service utilization:

***Pregnancy outcome*** is the proportion of pregnancies that results in neonatal (and maternal) deaths.

***Service utilization indicators*** are mainly the proportion of pregnancies that deliver by skilled birth attendants and those who access the EmONC facilities.

The comparison of these indicators between the intervention and control arms will determine the effectiveness of the interventions in terms of enhanced service utilization and reduced mortality.

### Study Setting

Two districts of Punjab i.e. Jhang and Khanewal have been selected for implementing the proposed trial. These are the districts where MNCH Programme or its partners have carried out the facility strengthening for EmONC services, have trained two or more batches of community midwives, and have a functioning network of lady health workers.

 · *Jhang* (recently divided into Jhang and Chiniot) is spread over an area of 8809 square kilometers, with an estimated population of about 3.5 million, and male to female ratio of 1.08. One quarter of the population is urban, whereas three quarters is rural. Total literacy rate is 37.12%, with 51.53% in males and 21.43% in females. The average household size is 6.5 with 85.9% dependency ratio. Currently married population is 62.2%.

 · *Khanewal* is spread over an area of 43494 square kilometers, with an estimated population of about 2,503,459 with 52% males and 48% females. The estimated population growth rate is 2.4%. The infant mortality rate is estimated to be 86/1000 which is higher than the provincial as well as the national figure of 77/1000. Total literacy rate is 45% and 33% of the population is living below poverty line. The crude birth rate is 21.5 and average household size is 6.9. It has four tehsils Khanewal, Mian Channu, Kabirwala and Jahanian.

### Study Population

In these two districts, there are about 26 EmONC facilities (tehsil head quarter hospitals (THQ) and rural health centers (RHC)), out of which *21* will be selected into the trial mainly on the basis of: a) general health care and EmONC service assessment, and b) both facility and community consent to participate in the trial. Each selected THQ and RHC, along with its associated BHUs and catchment population, will form a cluster for the trial. All pregnant women in these catchment populations (regardless of their age, social or medical profile) will be offered the services, as per the trial protocol.

### Data Management procedures

Most of the data will be collected as a part of the care delivery process by LHWs on the ‘Mother and Child Health Card’. The structured planning of safe birthing will be documented on specially designed ‘Birth Plan Form’. A copy of each of these birth plan data will be submitted to the respective health facility on a monthly basis, during the routine visit of the respective LHW. Each form will be reviewed for completeness, and those found with missing data will be acted upon accordingly. A sample of the filled/submitted forms will be cross-checked by the lady health supervisor (LHS), during her routine visit to the respective community. Similarly the transport facilitation plan will also be documented and records will be maintained.

EmONC service utilization and outcome data will be extracted from the relevant EmONC records being kept at the facilities. The EmONC data extracted from the facility record will also be cross-matched with data to be received from the respective LHWs. Research assistants will collect the data on monthly basis from the selected facilities in all the trail arms and send it to the central trial unit for data entry, cleaning and analysis.

Verbal autopsy will be conducted for 10% of the reported neonatal (and maternal) deaths, to understand their care experiences and the circumstances leading to death. A trained project staff, facilitated by the respective LHW, will carry out the verbal autopsy, within a month of the death being reported by the LHW. A specially designed tool will be used.

### Statistical considerations

The estimated required sample size for the trial is twenty one clusters. A strengthened EmONC facility (i.e. THQ and RHC) along with associated BHUs and catchment population (approximately 170,000) is taken as a ‘cluster’ for the trial. The required sample size has been estimated in light of internationally recommended procedure for field trial of health interventions [12]. This sample size gives 80% power to detect the assumed outcome differences (i.e. reduction in neonatal mortality by 25%) between the control and intervention arms. The acceptable confidence level is 95% and coefficient of variation in true proportion (k) is 0.17. Taking ICC as 0.0012, and loss to follow-up as 20%, at least 1,395 pregnant females will be required per cluster, at least 9,765 pregnant females per arm; a total of at least 29,295 pregnant females in the three trial arms.

The results in each cluster will be analyzed on the basis of “intention to treat”. This means the service utilization and pregnancy outcomes of each woman will be counted in the intervention for the cluster, regardless of her actually accepting or availing the offered services.

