The study size is adequate for valid measurement of differences in service utilization and neonatal mortality. However, to get valid measurement of differences in maternal mortality the required sample size is 66 (instead of 7) clusters per arm or 198 total in the trial (instead of 21). This more than ten-fold increase in sample size is not feasible to manage, so neonatal mortality is taken as the key pregnancy outcome indicator.

The proposed randomization does not allow asking and responding to individual preferences/convenience. So the trial will not answer the question what would happen if health services are able to offer intervention according to patient preferences/convenience. Further work will be needed to test the approaches sensitive to individual preferences, in the local programme setting.

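### The stated 80% power for a 25% reduction in neonatal mortality is not reached once the stated 20% loss is taken off: about 62–69% on k, or 68–75% on the ICC, assuming a baseline of 55/1000 and a two-sided test

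*Protocol article*

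**What the plan says.** The sample-size claim is in the protocol article under Statistical considerations: "This sample size gives 80% power to detect the assumed outcome differences (i.e. reduction in neonatal mortality by 25" per cent. The same paragraph gives two between-cluster inputs. First: "The acceptable confidence level is 95% and coefficient of variation in true proportion (k) is 0.17". Then: "Taking ICC as 0.0012, and loss to follow-up as 20%, at least 1,395 pregnant females will be required per cluster". The totals follow: "at least 9,765 pregnant females per arm; a total of at least 29,295 pregnant females in the three trial arms". It states neither a control-arm rate nor whether the test is one- or two-sided.

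The Methods part of the abstract makes clear that these are women at entry: "At least 29,295 pregnancies will be registered in the three arms, seven clusters per arm". It also says that analysis will be at cluster level. The only neonatal rate in the article is national and stands in the Background: "the newborn mortality is 55 deaths per 1000 live births".

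Under Addressing bias, error and limitations the article concludes: "The study size is adequate for valid measurement of differences in service utilization and neonatal mortality".

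**The concern.** A reader takes the 80% as applying to the design described: 7 clusters per arm, 1,395 women registered per cluster, one fifth lost. With the article's only neonatal rate and a conventional two-sided test, neither between-cluster input gives 80% at that size.

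Neonatal mortality is named as the key pregnancy outcome. If power is 62–75%, a true 25% reduction would be missed in 25–38% of such trials, against the 20% implied. A null result could then be read as stronger evidence against the interventions than it is, with the adequacy sentence in support.

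**Working it through.** **Inputs.** From Statistical considerations: 25% reduction, 95% confidence, k = 0.17, ICC = 0.0012, 20% loss, 1,395 per cluster. From the abstract: c = 7 clusters per arm. Assumed: control rate p0 = 0.055 (Background), so p1 = 0.75 × 0.055 = 0.04125; two-sided 5%. Analysed per cluster: m = 1,395 × 0.8 = 1,116.

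**Totals.** 7 × 1,395 = 9,765 and 3 × 9,765 = 29,295, as stated.

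**Formulas.** Power = Φ(√[(c − a)(p0 − p1)²/V] − 1.96). Here a = 0 is the normal approximation and a = 1 allows one extra cluster per arm for the small number of clusters. A t-test on 12 degrees of freedom was also computed, since analysis is at cluster level.
- k route: V = p0(1 − p0)/m + p1(1 − p1)/m + k²(p0² + p1²)
- ICC route: V = [p0(1 − p0)/m + p1(1 − p1)/m] × [1 + (m − 1) × ICC]

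**Recovering the plan's 80%.** Take the ICC route, all 1,395 analysed and a = 0. The design effect is 1 + 1,394 × 0.0012 = 2.673 and power is 78.4%. With the intervention rate rounded to 41/1000, power is 80.0% and the required cluster size is 1,397–1,401, against 1,395 stated. The match needs every registered woman to be analysed.

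**After the stated loss (m = 1,116).** (p0 − p1)² = 0.01375² = 0.00018906.
- k route: V = 0.00004657 + 0.00003544 + 0.0289 × 0.0047266 = 0.00021861. √(7 × 0.00018906/0.00021861) = 2.460, and 2.460 − 1.96 = 0.500, giving 69.2%. With a = 1: 62.5%. With the t-test: 61.8%.
- ICC route: design effect 1 + 1,115 × 0.0012 = 2.338, V = 2.338 × 0.00008201 = 0.00019174. √(7 × 0.00018906/0.00019174) = 2.627, giving 74.8%. With a = 1: 68.2%. With the t-test: 67.5%. With p1 = 41/1000 and a = 0: about 76%.

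| Analysed per cluster | Input | Normal | Added cluster | t-test |
|---|---|---|---|---|
| 1,116 | k = 0.17 | 69% | 62% | 62% |
| 1,116 | ICC = 0.0012 | 75% | 68% | 67–68% |
| 1,395 | k = 0.17 | 73% | 66% | 65% |
| 1,395 | ICC = 0.0012 | 78% | 72% | 71% |

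**Clusters per arm for 80% at m = 1,116**, from (1.96 + 0.842)² × V/(p0 − p1)²: 9.1 on k (10.1 with the added cluster) and 8.0 on the ICC (9.0).

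**Range over the assumed baseline (m = 1,116).** On k, power runs from 56–63% at 40/1000 to 67–75% at 80/1000 (t-test to normal). On the ICC route it reaches 80% at about 62/1000 (normal) or 72/1000 (added cluster).

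**Reduction detectable with 80% power from 55/1000.** About 28–30% on k and 27–29% on the ICC.

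**k against ICC.** ICC = k²p/(1 − p). At 55/1000: 0.0289 × 0.055/0.945 = 0.00168. At 41.25/1000: 0.0289 × 0.04125/0.95875 = 0.00124, which rounds to the stated 0.0012.

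**The case against.** The baseline and the sidedness are the reviewer's, not the sponsor's. The 55/1000 is a national figure per 1000 live births that the sample-size paragraph does not cite, and the trial outcome is a proportion of pregnancies. The Study Setting section puts Khanewal's infant mortality above the national level (86 against 77/1000). If neonatal mortality scaled likewise, the rate would be 55 × 86/77 = 61.4/1000, and the ICC route after loss gives 79.5% by the normal approximation. This stands for that variant. At the same rate the t-test gives 72.5%, and k gives about 64–71%.

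A one-sided 5% test after loss gives 83.7% on the ICC (78.4% with the added cluster) and 79.3% on k (73.7%). A one-sided ICC calculation with the added cluster and 41/1000 asks for 1,130–1,133 analysed, or 1,413–1,416 after dividing by 0.8, which is also near 1,395. An omitted loss allowance is therefore a likely explanation, not a proven one. The article nowhere mentions one-sided testing.

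The 1,395 is also a minimum. Applying Khanewal's crude birth rate of 21.5 to 170,000 people gives 3,655 births per cluster per year, or 2,924 after 20% loss. At that size the k formula needs 6.97 clusters per arm, or 7.97 with the added one. Larger clusters could thus bring k to 80% on the normal approximation, but the claim is attached to the minimum the article says is required.

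Two stronger readings are tempting. A reader might infer that k and the ICC contradict each other. They do not strictly: they differ at the control rate but agree after rounding at the intervention rate, and a constant k and a constant ICC cannot both hold exactly at two rates. A reader might also infer that neonatal mortality is the only outcome with a sample size. The limitations section gives one for maternal mortality as well (66 clusters per arm).

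**Conclusion.** The point holds in a limited form. With 7 clusters per arm, 1,116 analysed per cluster, an assumed baseline of 55/1000 and an assumed two-sided 5% test, power is about 62–69% on k and 68–75% on the ICC.

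The k result does not hinge on the baseline, since it stays below 80% throughout 40–80/1000. The ICC result does, since a baseline of 62–72/1000 would restore 80%. Under the two assumptions, the stated figure returns only on the ICC route with no loss.

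It would go too far to say that the plan's own inputs prove a shortfall, because two of the inputs needed are not stated. What the article supports is that its 80% does not follow from its k and its loss allowance at any baseline in that range with a two-sided test, and that its two between-cluster inputs give different power at the control rate.

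**What to change.** In Statistical considerations, state the baseline rate, the sidedness, one between-cluster measure (with the rate at which it applies), the formula, and whether 1,395 is before or after loss. Then restate the power. If the baseline is 55/1000, the test is two-sided and 1,395 is before loss, that is about 62–69% on k or 68–75% on the ICC. Alternatively, give the reduction detectable with 80% power: about 28–30% on k or 27–29% on the ICC. If the sponsor used another baseline or a one-sided test, state it and recompute.

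Amend the adequacy sentence under Addressing bias, error and limitations to match for neonatal mortality. If 1,395 was meant as the number analysed, the abstract's statement that 29,295 is the number registered must be reconciled with it.

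The correction needs no extra clusters or women. Its cost is a less favourable stated power or detectable reduction.
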